Beneficial to their self-management, patients are supported by a “smart assistant,” consisting of a tablet and electronic smart devices, which enable the patients to measure their vital parameters themselves when at home. Monitored vital parameters include blood pressure, pulse, body temperature, body weight, step count, saturation of peripheral oxygen, and, if necessary, blood sugar. Threshold values for these vital parameters are determined for each patient individually in line with evidence-based medical guidelines. The measured vital parameters are transferred to the electronic medical record once daily. Videos of the exercises taught by the physiotherapists during the hospital stay are retrievable on the tablet and allow patients to practice on their own after discharge. Furthermore, the tablet provides the patients with information about their diseases and the corresponding rationales for the specific treatments, the correct frequency and intake of the prescribed drugs, and general information on the importance of healthy nutrition and physical activity. Moreover, the tablet automatically reminds patients of their medication schedule via notification and requests digital confirmation of the intake. Finally, patients are asked to fill in a digital health diary, assessing the development of their subjective well-being, the occurrence and severity of various symptoms, and the level of self-efficacy.

Before patients are discharged from the hospital, the case manager coordinates the seamless continuation of the treatment plan in the ambulatory setting. In the first week after discharge, the case manager visits the patients in their home environment and ensures that all devices work properly. The patients continue their therapeutic exercises at home, supported by the videos on the tablet, and measure their vital parameters daily. The case manager inspects the vital parameters twice weekly and ascertains that none of the predefined thresholds is exceeded. The patient’s subjective well-being is ensured, additionally to the patient’s reported answers from the health diary, through weekly video calls between the case manager and the patient. The main contact person for health and medical-related questions during the period at home is the patient’s GP. Measured vital parameters along with other relevant health care information of each patient are reported once weekly via standardized reporting sheets in the electronic patient file to their GP.

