### Criteria for discontinuing or modifying allocated interventions {11b}

Each patient can decide to stop participation in the trial at any given point in time without any further explanations. A distinction is made here as to whether patients wish to withdraw from the intervention, the assessments or the consent to the transfer of health insurance data. If patients only wish to withdraw from the intervention and the assessments, the health insurance data used to determine the primary outcome can still be collected. The three home visits of the case manager should ideally take place until the end of the following week after discharge from the index hospital stay and subsequently 42 days (+ 5 working days) and 180 days (+ 10 working days) after the initial discharge. In case of unforeseen events (unplanned hospital admissions), the visits will be rescheduled to the next possible date.

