The following data will be obtained by A2 at the latest:Duration of index hospital stayDuration of stays in intensive or intermediate care units during the index hospital stayDuration of stays in other departments within the index hospital stay, if these departments are not part of the local eliPfad teamTransfers to external hospitals including geriatric facilitiesLength of stays in external hospitals including geriatric facilities after the index hospital stayTransfers to rehabilitation facilitiesDuration of stays in rehabilitation facilities

The following data are collected using collaborating statutory health insurance companies’ data at A3:Frequency and type of use of services in outpatient and inpatient care, drug prescription, remedies, and aids between T1 and T3Number of rehabilitation services between T1 and T3Number of transfers to “acute” geriatric units between T1 and T3Length of stay in inpatient facilities (incl. hospitals and rehabilitation facilities)Death between T1 and T3The sum of costs based on the above-defined service areas of collaborating health insurance companies’ data between T1 and T3

The following data will be collected by questioning the participants (if necessary, the relatives, the treating physicians) at all survey points (A0–A3):Quality of life using EQ-5D-5LDepression using the Geriatric Depression Scale (GDL)Geriatric assessment using the Multidimensional Prognostic Index (MPI)Timed up and go Test (TUG)De Morton Mobility Index (DEMMI)Minimal Nutritional AssessmentHealth status using the Self-Rated Health QuestionnaireSelf-efficacy (General Self-Efficacy Short Scale, ASKU)Medication planHealth literacyThe personal treatment burden

The following data will be collected at the survey points A0, A2, and A3:Patient-centeredness of care using PACIC

The following data will be collected at A1, A2, and A3:

Questioning about personal therapy goals / self-management

The following data are recorded at A2 and A3:Actual number of drugs taken by the patient at home using photo documentation

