**Clinical data collection**					
Evaluation of adverse events (AE)		X	X	X	X
Duration index hospital stay			X		
Duration stays in different wards			X		
Transfer to external hospitals			X		
Transfer to rehabilitation facilities			X		
MPI (geriatric assessment)	X		X	X	X
Health literacy		X	X	X	X
Quality of life/depression/health status/self-efficacy		X	X	X	X
Medication plan		X	X	X	X
Minimal Nutritional Assessment		X	X	X	X
Mobility tests		X	X	X	X
Patient orientation		X		X	X
Personal goals/self-management/personal therapy burden			X	X	X
Photo documentation drugs				X	X
Number of rehospitalizations				X	X
Health economic evaluation					X
Utilization of rehabilitation services					X
Length of stay in inpatient facilities					X
Death					X

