### Methods for additional analyses (e.g., subgroup analyses) {20b}

#### Analyses of safety-related aspects

Adverse events are assessed by relation, severity, and intensity; treatment comparisons are made in categories (e.g., MedDRA codes).

Changes in laboratory values are shown using shift tables; in addition, individual time courses are described and extreme values are marked in lists.

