### Adverse event reporting and harms {22}

No adverse events (AEs) in the strict sense are expected to be caused by the intervention. However, due to pre-existing (chronic) diseases, numerous complications are possible. In addition, the participants’ underlying diseases may worsen. These complications are not documented separately.

No novel or unapproved methods will be used as part of the intervention. Conceivably, a safety-related event could occur during independent home exercise; for example, a fall during a mobilization exercise. Events such as these and all other events that are not associated with the natural course of the pre-existing (chronic) diseases are documented as an AE. In case that such an event leads to hospitalization or death of the patient, it will be recorded as an SAE. AEs and SAEs will be recorded in the electronic data capture system (secuTrial® database) by the study team. AEs and SAEs will be identified by the study team during the weekly video calls between the case manager and the patient or during the assessments. SAEs will be immediately reported to the sponsor by the study teams.

Due to the open-label character of the trial, the obligation to document safety-related events begins in the intervention group at the time of enrollment and ends after the 6-week outpatient phase following the index inpatient stay at T2. There is no documentation requirement in the control group.

An overview of safety-relevant events will be provided to the ethics committee upon request after completion of the study.

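### The plan compares adverse events between the arms but requires them to be recorded in the intervention arm only

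*Protocol article*

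**What the plan says.** Three places in the protocol article bear on this.

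- **Analysis.** Methods for additional analyses {20b}, under Analyses of safety-related aspects: "Adverse events are assessed by relation, severity, and intensity; treatment comparisons are made in categories", with MedDRA codes given as an example of a category.
- **Collection.** Adverse event reporting and harms {22} places the duty to document safety events on the intervention group, from enrolment until the end of the six-week outpatient phase (T2). It gives the open-label design as the reason. For the other arm: "There is no documentation requirement in the control group". Events are to be found "during the weekly video calls between the case manager and the patient or during the assessments".
- **Schedule.** Table 1 (Participant timeline {13}) has a row beginning "Evaluation of adverse events (AE", marked at T0, T1, T2 and T3 with no restriction by arm.

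The video calls are described under Intervention description {11a}, where the eliPfad patient's well-being is followed "through weekly video calls between the case manager and the patient". Control patients receive standard care.

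**The concern.** The trial has two arms, so a treatment comparison of adverse events needs control-arm records. The protocol obliges nobody to create them. If the analysis is carried out as planned, the adverse-event table sets a monitored arm against one that is unmonitored or only partly monitored, and a difference in recording can be read as a difference in harm.

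This matters because eliPfad is proposed as a new standard of care if it proves effective, and no data monitoring committee or interim analysis is planned. The final adverse-event table could suggest a harm that the programme does not cause. It also could not credibly show a benefit, such as fewer falls.

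**Working it through.** The plan states no adverse-event rate, capture rate or test, so there is no figure of its own to reproduce. The check sets the rules side by side.

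**1. Who must be recorded, and when**

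| Source | Intervention arm | Control arm |
|---|---|---|
| Section {22} | Enrolment to T2 | No requirement |
| Table 1 | T0, T1, T2, T3 | T0, T1, T2, T3 (no arm split) |
| Section {20b} | Needed for the comparison | Needed for the comparison |

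Table 1 and section {22} disagree in two cells: the whole control arm, and T3 in the intervention arm. A site cannot follow both. Section {22} is the explicit statement and Table 1 does not override it.

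**2. How events are found**

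| Route in section {22} | Intervention arm | Control arm |
|---|---|---|
| Weekly video call | Yes, part of eliPfad | No |
| Assessments | Yes | Visits take place, but with no duty to record |

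Even if a site recorded control events voluntarily at the assessments, one route would be missing. Assessors also know the allocation (Who will be blinded {17a}), so discretionary recording cannot be assumed to be even.

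**3. What a comparison would then measure**

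Let the true risk be r in both arms, with capture a in the intervention arm and c in the control arm. Then

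apparent risk ratio = (r × a) / (r × c) = a / c.

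The true risk cancels and only recording remains. To show the range, *assume* r = 10% and a = 90% (neither is in the documents), with the planned 474 randomised per arm:

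| Assumed control capture c | Recorded, intervention | Recorded, control | Apparent risk ratio |
|---|---|---|---|
| 60% | 474 × 0.09 ≈ 43 | 474 × 0.06 ≈ 28 | 0.90 / 0.60 = 1.5 |
| 30% | ≈ 43 | 474 × 0.03 ≈ 14 | 0.90 / 0.30 = 3.0 |
| 0% | ≈ 43 | 0 | undefined |

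Every row has equal true risk.

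**4. Can the analysis stage repair it?**

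No. An analysis plan cannot restore control events that were never recorded. The insurer data listed under Outcomes {12} cover "use of services in outpatient and inpatient care, drug prescription, remedies, and aids", together with death, lengths of stay and costs. They do not hold adverse events graded by relation or intensity.

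**5. Does it reach the primary result?**

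No. Rehospitalisations come mainly from insurer data in both arms and do not depend on adverse-event recording.

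**The case against.** The strongest reply is that an absent requirement is not a prohibition. Assessments take place in both arms, Table 1 lists adverse-event evaluation without an arm split, and some control events may therefore be recorded. This stands in part: control counts may be incomplete rather than exactly zero. It does not rescue the comparison, because capture would still be unequal and would vary with which rule each site followed.

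A second reply is that the important safety outcomes are already compared. This stands. Statistical methods {20a} covers unplanned readmissions as the primary outcome, time to death by Cox regression, and intensive care and external hospital stays by the primary-outcome method. Section {20b} adds laboratory shift tables, and laboratory values are scheduled at A0 to A3 without arm restriction. A reader might infer that the trial has no valid between-arm safety information; the documents do not support that.

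Three further inferences are tempting but unsupported:

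- **A specific false-positive rate or p-value.** The plan names no test for adverse events and gives no event rates, so any such figure would illustrate assumptions rather than measure the defect.
- **A ready-made comparison by diagnosis group.** The article does not list main diagnosis among the insurer variables. For patients of other insurers the source is the patient receipt, whose diagnostic content is not described.
- **A faulty event definition.** Besides exercise-related events, section {22} provides that "all other events that are not associated with the natural course of the pre-existing (chronic) diseases are documented as an AE", which exempts expected disease course. For multimorbid patients in a low-risk, non-drug programme this is a stated design choice, not a contradiction.

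Condensation into an article is no defence either, since both conflicting statements are made outright.

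**Conclusion.** The contradiction holds. The planned between-arm comparison of adverse events cannot validly be made from the records the protocol requires, and Table 1 adds a second inconsistency, on arm and on T3. The likely error is a spurious excess under eliPfad. Its size is the ratio of capture between the arms, which the documents do not allow anyone to estimate; the 1.5 and 3.0 above rest entirely on assumed capture.

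The consequence is limited to the harms table. The primary rate ratio is not biased, no interim decision depends on these records, and the both-arm outcomes already planned remain usable. The point should be corrected, but it does not threaten the trial's main conclusion.

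**What to change.** 1. In Analyses of safety-related aspects, remove the treatment comparison of adverse events. State that adverse and serious adverse event records are reported descriptively for the intervention arm only.
2. In Table 1, restrict the adverse-event row to the intervention arm and to T0 to T2, in line with section {22}.
3. State that between-arm safety conclusions rest on outcomes already planned for both arms: unplanned readmissions, time to death, intensive care and external hospital stays, and laboratory shift tables.

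**Cost.** Rewording of one paragraph and one table row, with no new data collection and no change to the primary analysis. The insurer-based outcomes also hold up under partial withdrawal: for patients leaving only the intervention and assessments, "the health insurance data used to determine the primary outcome can still be collected". Under section {25} the change must be communicated to the ethics committees.

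**Limits.** Non-serious events, including falls during home exercise (the very harm section {22} gives as its example), stay uncompared. Insurer-recorded deaths cover T1 to T3 only, so a death between randomisation and discharge would not appear there. Index-stay intensive care days can include days before randomisation, so they are weak evidence on the in-hospital phase.

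**Alternative.** Keeping the comparison would need the same definitions, window and detection route in both arms, for example a standard query at A1, A2 and A3. Enrolment began on 09/01/2023, so this would be a mid-trial change, and controls already past those visits would have no equivalent records. The rewording is the proportionate choice.

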### Frequency and plans for auditing trial conduct {23}

Authorized representatives of national or local authorities will be permitted to inspect or audit facilities and records relevant to this study. In addition, at the steering committee meetings (see item 5d), the progress of the study and emerging problems are discussed, and strategies for solving these problems are implemented.

### Plans for communicating important protocol amendments to relevant parties (e.g., trial participants, ethical committees) {25}

The sponsor and principal investigator may modify or propose modifications to the study protocol. Substantial changes will be made only after deliberation by the ECs. In emergencies, deviations from the study protocol may be made to protect the rights, safety, and welfare of subjects without prior approval of the Sponsor and the ECs. Such deviations will be documented and communicated to the Sponsor and the ECs as soon as possible. All non-substantial changes will be communicated to the ECs.

### Dissemination plans {31a}

The results of this study are intended for open-access publication in high-impact peer-reviewed journals read by medical professionals, as well as those working in the field of public health. In addition, the results will be presented in the form of oral presentations and posters at major relevant national and international conferences.

## Discussion

This trial is the first within the German healthcare system to investigate the effectiveness of a new model of care for multimorbid, frail elderly who are at high risk of readmission after hospitalization. Given the current inadequate care for this vulnerable group of patients, eliPfad could become a new standard of care if it lowers the treatment burden and proves to be (cost-)effective, by leading to fewer readmissions. This way it benefits both society and the German health care system by improving overall quality of care and potentially saving health expenditures.

There are some limitations associated with this trial that need to be mentioned. First, due to the nature of eliPfad, it is not possible to blind patients and investigators. This may lead to observer bias on the part of the investigators and increase the dropout rate of patients who have been assigned to the control group and are no longer willing to participate. To address these issues, standard operating procedures (SOPs) will be established to minimize observer bias, and evaluators will be blinded to the results. The assumed higher dropout rate in the control group will be compensated for by increasing the sample size accordingly to account for the higher dropout rate without losing power for the main objective.

A second limitation is that patients in both groups, i.e., the intervention and control groups, are treated in the same wards at baseline, and patients in the control group may receive similar treatment as those in the intervention group. To avoid this form of contamination bias, SOPs are established for all participating professional groups. In addition, the case manager is not present on the ward regularly, but only to see the patients in the study.

## Trial status

The study protocol (version 1.1, 10 August 2023) has been approved by the ethics committee of the University Hospital Cologne. The trial was registered in the DRKS (German Clinical Trials Registry) on 08/14/2023 under the ID DRKS00031500 (https://drks.de/search/en/trial/DRKS00031500). The study will be conducted following the principles of the Declaration of Helsinki. The first patient was enrolled on 09/01/2023. Recruitment will take place over 2 years and runs until 08/31/2025, accordingly. The end of the study is defined as the date on which the (last) A3 assessment was performed on the last patient, which is expected to be in March/April 2026.

## Data Availability

The participating statutory health insurance companies will provide well-defined data to answer the objectives. Every study center can access and enter the data for the trial participants at their center. The evaluators receive all data in pseudonymized form for the final evaluation. The exact procedure for data collection and data entry, as well as access to the data, will be defined in an agreement between all institutions involved in eliPfad.

## Abbreviations

A: Assessment
ASKU: Short Scale for Measuring General Self-Efficacy Beliefs
CCM: Chronic Care Model
DRKS: Deutsches Register Klinischer Studien
CHD: Coronary heart disease
CKD: Chronic kidney disease
COPD: Chronic obstructive pulmonary disease
DEMMI: De Morton Mobility Index
DGCC: Deutsche Gesellschaft für Care und Case Management
DM: Diabetes mellitus
DMC: Data monitoring committee
eCRF: Electronic case report form
EDC: Electronic data capture
e-ePA: Cross-sector electronic patient record
EQ-5D-3L: European Quality of Life 5 Dimensions 3 Level Version
FORTA: Fit fOR The Aged
G-BA: Gemeinsamer Bundesausschuss
GDS: Geriatric Depression Scale
GP: General practitioner
MAR: Missing-at-random
MDM: Minimal disruptive medicine
MPI: Multidimensional Prognostic Index
MRC: Medical Research Council
NMAR: Not-missing-at-random
NYHA: New York Heart Association
PACIC: Patient Assessment of Chronic Illness Care
PAD: Peripheral artery disease
PI: Principal investigator
RCT: Randomized controlled trial
SAP: Statistical analysis plan
SOP: Standard operating procedure
T: Time point
TUG: Timed up and go Test
